## Analysis of Demographics

Demographic characteristics (age, sex, race) of each study cohort will be tabulated.

## Analysis of Safety

The overall percentage of subjects reporting solicited and unsolicited AEs will be tabulated by type of event, by severity and by relationship to the investigational product.

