## Potential Risks and Benefits

There will be no direct benefit to study participants enrolled in this study, however the data produced may benefit future populations in directing product use to prevent infection with HIV or HSV-2.

It is anticipated that there will be minimal risks to study participants. There may be mild vaginal or cervical irritation associated with insertion and removal of the INSTEAD® SoftCup and slight discomfort associated with the drawing of blood samples. In addition, there may be effects as detailed in Section 6.9.

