## Number of Subjects

A total of 12 eligible subjects are to be enrolled into the study.

Drop-outs (as defined in Section 9) can be replaced at the discretion of the Sponsor.

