# STUDY PROCEDURES AND EVALUATIONS

This is a single-centre, open-label, randomised, cross-over, Phase 1 study.

After providing one screening and three pre-dose cervico-vaginal (CV) samples, each subject will receive 5 single doses of 3% SPL7013 Gel with at least 5 days washout between doses. CV samples will be taken at 0 (between 2 and 10 minutes), 1, 3, 12 and 24 hours after dosing in a randomised sequence and a further sample at the follow-up visit as shown in Figure 2.

All study visits will be scheduled such that they do not fall within 2 days before and 5 days after the expected onset of menses. Product administration and CV sampling is not to take place during menstruation.

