## Study Procedures

## Pre-dose sampling

Following enrolment the participants will be given three CV sampling kits and asked to provide three separate samples from three separate days. The samples should be taken at least 24 hours apart during the intra menstrual period (i.e. should not include menses). The participants will not be required to attend the study centre and will be able to send the samples into the clinical unit by courier, however if they experience difficulty undertaking the sampling, they may attend the clinical unit and be assisted by female staff. The courier will be in the form of a taxi service, regularly used by the clinical study site for this function, and the sample will be stored in refrigerated conditions on ice packs in an opaque, insulated container during transit. The sample will be marked as an uninfected biological sample; however the nature of the sample will not be identifiable to the courier to protect the privacy of the study subject. The sample is to be transported to the study centre within 24 hours of collection, if not; the sample is to be repeated.

During this period, any AEs reported will be recorded as screening/baseline signs and symptoms, and medications recorded as concomitant medication.

## Treatment Period 1

The first treatment period will include the following procedures:

- Review of the inclusion/exclusion criteria
- Review of screening/baseline signs and symptoms pre-dose and AEs post dose and concomitant medications
- Pregnancy test
- Randomisation to a sampling sequence
- Condom and sexual restrictions counselling (see Section 7.4.4)
- Administration of 3% SPL7013 Gel by study participant. If the study participant is not considered to be able to administer the product correctly after training during screening, or is uncomfortable doing so, a female member of the study team may administer the product.
- CV sampling using the INSTEAD SoftCup at 0, 1, 3, 12 or 24 h post application according to the randomization schedule. A time window of within 5 minutes is permissible for the 0 and 1 hour time points, and within +/-10% of the time for the 3, 12 and 24 hour time points (see Section 7.2.1)

Study participants will be permitted to leave the clinical unit between study treatment administration and CV sampling, except when a time 0 or 1 hour sample is to be collected. If necessary, study participants may stay overnight at the clinic.

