***Grade 4: Life Threatening*** An AE that causes inability to perform basic self-care functions or medical or operative intervention is indicated to prevent permanent impairment, persistent disability or death.

***Grade 5: Death*** An AE that results in death.

It should be noted that an AE that is considered to be “severe” may not necessarily be considered to be “serious” or of major medical significance.

The relationship to study drug therapy should be assessed using the following definitions:

***Not Related*** The adverse event is clearly explained by another cause not related to the study agent.

***Probably Not Related*** A potential relationship between study agent and the adverse event could exist (i.e. the possibility cannot be excluded), but the adverse event is most likely explained by causes other than the study agent.

***Possibly Related*** The adverse event and administration of study agent are reasonably related in time, and the adverse event can be explained equally well by causes other than the study agent.

***Probably Related*** The adverse event and administration of study agent are reasonably related in time, and the adverse event is more likely explained by study agent than other causes.

***Definitely Related*** The adverse event and administration of study agent are related in time, and a direct association can be demonstrated.

It should be emphasized that ineffective treatment should not be considered as causally related in the context of AE reporting.

These criteria in addition to good clinical judgment should be used as a guide for determining the causal assessment.

The degree of certainty with which an adverse event is attributed to study drug/product treatment or alternative cause, (e.g. natural history of the underlying diseases, concomitant therapy, etc) will be determined by how well the event can be understood in terms of:

- Known pharmacology of the product.
- Reaction of a similar nature previously observed with similar products/drugs.
- The event having often been reported in literature for similar products as product related.
- The event being related by time to product/drug administration/ termination, product/drug withdrawal, or reproduced on rechallenge.

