## EAE Reporting Requirements for this Study

EAE Reporting Level

This study uses the Intensive Level of EAE reporting as defined in the DAIDS EAE Manual.

Study Agents for Expedited Reporting to DAIDS

The study agents that must be considered in determining relationships of AEs requiring expedited reporting to DAIDS are: 3% SPL7013 Gel, applicator and INSTEAD SoftCup.

Study Agents for Expedited Reporting to Starpharma Pty Ltd

The study agents that must be considered in determining relationships of AEs requiring expedited reporting to Starpharma Pty Ltd are: 3% SPL7013 Gel.

Grading Severity of Events

The severity of adverse events will be graded according to Section 8.3.

EAE Reporting Periods

AEs must be reported on an expedited basis at the Intensive Level during the Protocol-defined EAE Reporting Period, which is:

The entire study duration for an individual participant (from study enrolment until study completion or discontinuation of the participant from study participation for any reason).

After the end of the Protocol-defined EAE Reporting Period stated above, the site must report serious, unexpected, clinical suspected adverse drug reactions if the study site staff becomes aware of the event on a passive basis, i.e., from publicly available information.

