## Sample Size Estimation

Twelve participants have been chosen for an initial evaluation of the retention of SPL7013 amount and antiviral activity over time after application of SPL7013 Gel. No formal statistical determination has been performed as these parameters have not been previously assessed and therefore no information exists about the variability of these endpoints. The number of study participants has been chosen as a reasonable number for an initial assessment of the primary endpoints.

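### The routine adverse-event assessment and the planned safety table ask about the gel only, so they cannot separate SoftCup irritation from gel irritation, although the design supplies cup-only placements to compare with

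*Protocol*

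**What the plan says.** **Shared expected event.** Protocol 2.4 states: "There may be mild vaginal or cervical irritation associated with insertion and removal of the INSTEAD® SoftCup". Section 6.9 (Warnings) puts vaginal and cervical irritation first among the events that may follow the gel.

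**Placements.** Section 7 states: "After providing one screening and three pre-dose cervico-vaginal (CV) samples, each subject will receive 5 single doses of 3% SPL7013 Gel". Section 7.2.1 fixes one cup sample per application. The 0 h sample is taken 2 to 10 minutes after the gel. Section 7.1.2.4 adds one cup sample at follow-up, at least a week after the last dose. There is no placebo arm (2.2).

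**Causality.** Section 8.3 judges relationship to the study drug or agent on a five-level scale. Possibly Related applies when the timing fits and "the adverse event can be explained equally well by causes other than the study agent". Two lower levels, Probably Not Related and Not Related, are available when another cause is more likely or clear. The examples of other causes in 8.3 are underlying disease and concomitant therapy; the sampling device is not mentioned. For expedited reports to DAIDS, 8.7.2 lists the agents to consider as "3% SPL7013 Gel, applicator and INSTEAD SoftCup". For expedited reports to the sponsor it lists the gel alone.

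**Events before dosing.** In the pre-dose sampling period (7.1.2.1), "any AEs reported will be recorded as screening/baseline signs and symptoms". Table 1, footnote 8, says the same of anything reported before the first dose. Section 8.2.1 starts adverse-event reporting at first dose, whereas 7.3.4 has all events from consent recorded in the CRF.

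**Analysis.** Section 10.6 gives one sentence: the percentage of subjects with adverse events "will be tabulated by type of event, by severity and by relationship to the investigational product".

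**The concern.** Local tolerability is part of the secondary objective (3.2). After each dose a woman has been exposed to both gel and cup, and both are expected to cause the same complaint. With no placebo arm, the cup-only placements are the only comparator inside the study.

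The recording rules treat the two situations differently. Irritation after gel plus cup is an adverse event scored against the gel. The same irritation after a cup-only placement before dosing is a baseline sign. The routine adverse-event assessment does not ask whether the cup was the cause, although 8.7.2 shows that the sponsor regards it as a possible one. The mild irritation described in 2.4 would ordinarily be handled by routine recording, where the cup is not asked about.

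At stake is the reading of the tolerability result. A count of possibly related genital events could reflect the gel, the sampling device or both, and the planned table gives no means of telling which.

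**Working it through.** The protocol has no figure of its own to reproduce: "A total of 12 eligible subjects are to be enrolled into the study", and 10.3 explains "No formal statistical determination has been performed as these parameters have not been previously assessed". It gives no rate of cup irritation either.

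**Step 1: count the placements (7, 7.1.2.4, 7.2.1).**

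| Type of placement | Per woman | In 12 women | How events are recorded |
|---|---|---|---|
| Cup only, before dosing (1 screening + 3 pre-dose) | 4 | 48 | Baseline signs and symptoms |
| Gel plus cup (Periods 1–5) | 5 | 60 | Adverse events |
| Cup only, follow-up | 1 | 12 | Adverse events |

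Section 7.2.1 asks for at least one screening sample, so four is a minimum. Of the 60 cup-only placements, 48 (48/60 = 80%) have their events classed as baseline signs. The other 12 lie in the adverse-event window, but at the last visit, so events starting afterwards may be missed.

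**Step 2: follow one irritation through the rules.**
- After gel plus cup, it is an adverse event assessed against the gel. If the investigator finds cup and gel equally plausible, 8.3 gives Possibly Related. If the cup seems more likely, 8.3 gives one of the two lower levels. In neither case does 8.3 ask for the cup to be scored as a cause.
- After a cup-only placement before dosing, it is a baseline sign. Section 10.6 does not state its window. That such events stay out of its table follows from 7.1.2.1, footnote 8 and 8.2.1 together, while 7.3.4 points the other way.

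**Step 3: how large could the mixing be?** Let p be the chance that one cup placement irritates. Assume that placements are independent, the gel has no effect, and every cup irritation after a dose is scored related. The share of women with at least one event is 1 − (1 − p)^k over k placements; multiplying by 12 gives the expected number of women. All values of p are assumptions.

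| Assumed p | Five dosed placements, 1 − (1 − p)^5 | Women of 12 | Four pre-dose placements, 1 − (1 − p)^4 | Women of 12 |
|---|---|---|---|---|
| 1% | 4.9% | 0.59 | 3.9% | 0.47 |
| 2% | 9.6% | 1.15 | 7.8% | 0.93 |
| 5% | 22.6% | 2.71 | 18.5% | 2.23 |
| 10% | 41.0% | 4.91 | 34.4% | 4.13 |
| 20% | 67.2% | 8.07 | 59.0% | 7.08 |

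**Step 4: relax the scoring assumption.** If only a fraction f of cup irritations is scored related, the share is 1 − (1 − fp)^5. At p = 5%:
- f = 50%: 1 − 0.975^5 = 11.9%, or 1.4 of 12 women.
- f = 25%: 1 − 0.9875^5 = 6.1%, or 0.7 of 12 women.

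The five-dose figures in Step 3 are therefore upper bounds for each p. The four-placement columns show that, with an inert gel, a side-by-side table would be expected to show nearly as much irritation without gel as with it.

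**The case against.** A reader might infer that the protocol automatically counts cup irritation as gel intolerance, that the cup-only information is lost, and that even an inert gel must show related events. The documents do not support this.

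- **Scoring is a judgement.** Section 8.3 offers two lower levels and calls for good clinical judgement, and 2.4 already names the cup as a cause. Possibly Related is one plausible outcome, not a fixed one.
- **The data survive.** Table 1 marks adverse-event collection at screening and pre-dose, the events are recorded as baseline signs, and Period 1 includes their review. Section 8.1.1 counts worsening of a pre-existing condition as an adverse event.
- **Not all gel-free use is set aside.** The follow-up placement stays in the adverse-event window.
- **Timing helps.** Where sampling comes hours after the gel, irritation that starts before the cup is inserted cannot come from that period's cup. At 0 h this helps very little.
- **The contrast is imperfect.** The pre-dose samples are meant for assay validation, are mostly taken at home, and follow a training placement. Order, learning and setting are confounded with gel exposure.
- **The consequence is limited.** Of the pausing criteria, one needs grade 3 or higher genital events, and the others need ulceration or discontinuations considered related. Expected cup irritation is described as mild. Any misattribution counts against the product, and the study plans no safety test.
- **A table layout may sit in an analysis plan that is not shown.**

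These points stand and limit the size of the problem. They do not remove it. An extra table can wait for the analysis plan, but attribution to the cup cannot: if the adverse-event page asks only about the study drug, no later analysis can recover it.

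**Conclusion.** The concern holds as a limitation of the recording rules and the planned safety table. Cup and gel share an expected event and occur together at every dose. Routine causality and the 10.6 table refer only to the study drug or product, and events at 80% of the cup-only placements are classed as baseline signs. As planned, the table cannot separate cup from gel effects on local tolerability.

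The size is unknown because the protocol gives no cup-irritation rate. The 9.6%, 22.6% and 41.0% of women at assumed risks of 2%, 5% and 10% rest on an inert gel, independent placements and every cup irritation being scored related. They show what is possible and are not a forecast.

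The protocol also treats the agents inconsistently: gel, applicator and SoftCup for DAIDS reports, gel alone for expedited reports to the sponsor, gel or applicator in the expedited-event row of Appendix 16.3, and the product alone in 10.6. It conflicts on when adverse-event collection starts (7.3.4 against 8.2.1). The change is worth making because it is cheap and serves a stated objective; the trial is not invalid without it.

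**What to change.** 1. In 8.3, have the adverse-event page record relationship to gel, applicator and SoftCup separately, using the agents already listed in 8.7.2. Record onset relative to gel application and to cup insertion. Tabulate these relationships in 10.6.
2. In 10.6, add a descriptive within-woman table of genital signs and symptoms per placement: cup-only (screening, three pre-dose, follow-up) beside gel-plus-cup (Periods 1–5). With 12 women this sets 60 placements beside 60. State that order, training and home versus clinic setting are confounded with gel exposure, so no formal test is intended.
3. Reconcile 7.3.4 (from consent), 8.2.1 (from first dose), and 7.1.2.1 with Table 1 footnote 8 (baseline signs), and state which events enter the 10.6 table.

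The cost is a few added fields on the adverse-event page, one further table and a clarifying edit. No visit, sample or procedure is added.

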## Interim Analysis

No interim analyses will be conducted during the study.

# HUMAN SUBJECTS PROTECTION

## Regulatory Considerations

Starpharma or its agent will submit the appropriate documents to the local regulatory agencies and IEC/IRBs and will await approval prior to study commencement.

This study will be conducted in accordance with the following guidelines and regulations:

- International Conference on Harmonization (ICH) Guidelines for Good Clinical Practice (GCP) (E6)
- ICH Guidelines for Good Clinical Practice annotated with TGA comments (July 2000)
- NHMRC “National Statement on Ethical Conduct in Research Involving Humans”
- The Declaration of Helsinki
- US FDA Human Subject Protection Regulations (Title 21 Code of Federal Regulations (CFR), Parts 50, 54, 56 & 312, and Title 45 CFR Part 46)
- NIAID Clinical Terms of Award (<http://www.niaid.nih.gov/ncn/pdf/clinterm.pdf>), and other guidance (<http://grants.nih.gov/grants/guide/notice-files/NOT-OD-00-039.html>, and <http://grants.nih.gov/grants/guide/notice-files/NOT-OD-00-038.html>).

## Independent Ethics Committee (IEC)/Institutional Review Board (IRB)

Prior to the commencement of the clinical study, written IEC/IRB approval from the Alfred Hospital Ethics Committee must be received by the Investigator. Subject recruitment will not start until satisfactory evidence of ethical approval is given by the Investigator to Starpharma in writing. Starpharma requires written approval that clearly identifies the study protocol by title, number, and version date. The study site must have copies of the IRB procedures and roster (or a statement of appropriate constitution of the IRB) in their Study File.

## Interpretation of the Protocol / Protocol Amendments

With the exception of emergency situations, no changes or deviations in the conduct of the signed protocol will be permitted without the prior documented approval of Starpharma, the Starpharma Medical Monitor/responsible physician, DAIDS Medical Officer and the IEC/IRB. In the event of an emergency, the Investigator will institute any medical procedures deemed appropriate. However, all such procedures must be promptly reported to Starpharma, the Starpharma Medical Monitor/responsible physician and the IEC/IRB.

Administrative changes of the protocol are defined as minor corrections and/or clarifications that have no effect on the way the study is to be conducted. These administrative changes will be agreed upon by Starpharma, the DAIDS Medical Officer and the investigator and will be documented in a memorandum. The IEC/IRB will be notified of administrative changes by the investigator. Starpharma will submit the clarification memo to the DAIDS Medical Officer.

Following approval of protocol amendments, an amended final protocol will be prepared.

## Subject Informed Consent

Written informed consent will be obtained from all potential study participants prior to the initiation of any study-related procedures. In obtaining and documenting informed consent, the investigators will comply with applicable local and domestic regulatory requirements and will adhere to GCP and to the ethical principles that have their origin in the Declaration of Helsinki.

Prior to the beginning of the trial, site investigators will have the IRB/EC’s written approval/favourable opinion of the protocol, informed consent forms, and any other study-related information to be provided to participants. This study does not plan to enrol children under 18 or illiterate individuals. All study related materials including the informed consent forms will be available in English.

The informed consent process will give individuals all of the relevant information they need in order to decide whether to participate, or to continue participation, in this study. Potential research participants will be permitted to ask questions and to exchange information freely with the study investigators. Only listed study investigators may obtain informed consent from potential study participants. The investigators will keep research participants fully informed of any new information that could affect their willingness to continue study participation.

## Confidentiality

Members of the study staff sites are all trained in subject confidentiality. The log of study participant names and other protected health information will be kept in a double-locked area. All computer information about study volunteers will be kept on a computer with log-on passwords. Laboratory specimens are labelled with study numbers and date, and are delivered or shipped by study staff. The study sites’ data management and clinical staff are the only personnel with access to the protected health information of study volunteer. Each member of the staff has a log-on identification and password, logs off before leaving a computer screen unattended, and closes their office door when out of the office. All research records will be kept indefinitely following closure of the study.

Starpharma will preserve the confidentiality of subjects taking part in this study. In the event of names inadvertently appearing on study documentation, this information will not be processed.

Subject medical records pertaining to this study may be inspected/audited at any time by Starpharma employees or their duly authorised representatives, a regulatory authority or the IEC/IRB. All records accessed will be strictly confidential. Consent to participate in this study includes consent to these inspections/audits.

# ADMINISTRATIVE ASPECTS

## Clinical Trial Agreement

Prior to commencement of the study, the Investigator must sign a clinical trial agreement that will clearly delineate the responsibilities and obligations of investigator and sponsor and will form the contractual basis under which the clinical trial will be conducted.

A Clinical Trial Agreement will also be put in place between DAIDS and Starpharma.

